## Abstract

**Background:**

Almost 90% of residents living in long-term care facilities have limited mobility which is associated with a loss of ability in activities of daily living, falls, increased risk of serious medical problems such as pressure ulcers, incontinence and a significant decline in health-related quality of life. For health workers caring for residents it may also increase the risk of injury. The effectiveness of rehabilitation to facilitate mobility has been studied with dedicated research assistants or extensively trained staff caregivers; however, few investigators have examined the effectiveness of techniques to encourage mobility by *usual caregivers *in long-term care facilities.

**Methods/Design:**

This longitudinal, quasi-experimental study is designed to demonstrate the effect of the sit-to-stand activity carried out by residents in the context of daily care with health care aides. In three intervention facilities health care aides will prompt residents to repeat the sit-to-stand action on two separate occasions during each day and each evening shift as part of daily care routines. In three control facilities residents will receive usual care. Intervention and control facilities are matched on the ownership model (public, private for-profit, voluntary not-for-profit) and facility size. The dose of the mobility intervention is assessed through the use of daily documentation flowsheets in the health record. Resident outcome measures include: 1) the 30-second sit-to-stand test; 2) the *Functional Independence Measure*; 3) the *Health Utilities Index Mark 2 and 3; *and, 4) the *Quality of Life - Alzheimer's Disease*.

**Discussion:**

There are several compelling reasons for this study: the widespread prevalence of limited mobility in this population; the rapid decline in mobility after admission to a long-term care facility; the importance of mobility to quality of life; the increased time (and therefore cost) required to care for residents with limited mobility; and, the increased risk of injury for health workers caring for residents who are unable to stand. The importance of these issues is magnified when considering the increasing number of people living in long-term care facilities and an aging population.

**Trial Registration:**

This clinical trial is registered with ClinicalTrials.gov (trial registration number: NCT01474616).

## Background

Immobility is a major factor contributing to a reduced quality of life and preventable adverse events among older adults living in residential long-term care (LTC). Of the more than 150,000 older Canadians living in LTC facilities [1] almost 90% have some type of reduced mobility, [2] with approximately 40% of LTC residents with dementia losing their ability to walk annually [3,4]. Immobility leads to a loss of ability in activities of daily living (e.g. dressing or toileting), increased risk of falls and medical problems such as pressure ulcers and incontinence [5-9]. Although the adverse consequences of immobility and bed rest have been known for many years, elderly residents living in LTC facilities still commonly sit in wheelchairs or lie in bed for prolonged periods of time, in many cases for most of their waking hours [10,11].

When a resident loses the ability to stand up from a chair, the bed, or a toilet, both the time and the cost of health care escalate dramatically [12,13]. Transferring the resident then involves seeking a second health care aide to assist and often retrieving a mechanical lift to assist with the transfer. In the resource constrained environment of LTC, the extra time required for a transfer may translate to fewer transfers, significant delays in toileting (if toileted at all), and higher risk for a host of adverse consequences associated with immobility. Inactivity significantly affects quality of life for LTC residents in terms of ability to walk, balance and transfer [14-16].

Residents' immobility has ramifications on the nature of the work in LTC. Increased resident dependency increases the workload for health care aides as they perform more lifting and thereby heightens their risk of injury [17,18]. Approximately 60% of the loss of ability to walk in residents with dementia is potentially treatable [4]. The effectiveness of rehabilitation to facilitate mobility has been studied in LTC settings with dedicated research assistants or extensively trained staff caregivers [19-30]; however, the evidence that such rehabilitative approaches will be transferred, accepted, or sustained in the typically resource constrained environments of contemporary residential LTC facilities is lacking [31-33]. Few investigators have examined the effectiveness of techniques to encourage mobility by the usual caregivers in these settings, that is, by the unregulated health care aide workforce.

The primary purpose of this study is to determine if a simple mobility innovation (the sit-to-stand activity), implemented within the context of routine care activities of health care aides, can maintain or improve the mobility, function, and health-related quality of life of residents with dementia in LTC facilities.

We have selected our mobility intervention to be the sit-to-stand activity based on: a) the feasibility of integrating it into the daily practices of health care aides and residents using existing resources; b) preliminary evidence which supports integrating activity into functional situations such as dressing, toileting, or walking rather than introducing an exercise [27,34]; and, c) evidence suggesting that performance of the sit-to-stand activity may delay the well known trajectory of functional decline in LTC residents [24,32,34-38]. The sit-to-stand activity is thought to be one of the most mechanically demanding for LTC residents [39], yet it is still considered to be a low intensity exercise. Low intensity exercise has been found to improve physical performance [40,41] and activities of daily living [40,42,43] among frail older adults in LTC facilities although high intensity exercise did achieve a greater effect [40].

The benefits of implementing this simple sit-to-stand activity are seen at several levels. The intervention is low cost, does not require any specialized staff, training or equipment nor does it involve an important increase in the time required to care for residents; thus the mobility intervention possesses most of the attributes of successfully adopted innovations [44]. At the level of the health care aide and resident, standing up from a chair has the following attributes: relative advantage (does not require extensive training); compatibility (is consistent with activity in existing routines); low complexity (is a simple activity); trialability (can be easily tried and customized to individual residents); and, observability (improved mobility was visible to some health care aides during the pilot study).

Prior to the development of this protocol we completed a pilot study to assess the effect of the uptake of the sit-to-stand mobility intervention by health care aides on the mobility of LTC residents with dementia. This enabled us to: (1) assess the feasibility of integrating a simple activity into the daily work of health care aides; (2) develop a method of monitoring the adherence of health care aides to the activity; (3) calculate an appropriately powered sample size; and (4) begin to assess the response of this frail LTC population to the mobility intervention [34]. In the pilot study we assessed the mobility of 32 residents at baseline and after four months of exposure to the sit-to-stand intervention with the assistance of health care aides on day and evening shifts. Residents completed a mean of 29.7 (SD = 20.79; range 2 to 76) occasions of sit-to-stand repetitions in the month prior to the measurement of their sit-to-stand performance. For every 12 occasions of repeating the sit-to-stand exercise that month, the odds of improving or maintaining performance with the 30-second sit-to-stand test doubled (p = 0.02). This early finding with a small sample provides promising evidence that exposure to the sit-to-stand functional activity carried out in the context of daily care with health care aides may delay the loss of ability to transfer in nursing home residents with dementia [45]. We hypothesize that this ability to transfer will positively influence the resident's overall mobility, function and health-related quality of life.

Our research question is: What is the effect of the sit-to-stand mobility intervention on the mobility, function, and health-related quality of life of LTC residents with dementia?

## Methods/Design

This is a longitudinal quasi-experimental study designed to demonstrate the effect of the sit-to-stand intervention on the mobility, function, and health-related quality of life of LTC residents with dementia (Figure 1).

**Figure 1 F1:**
[figure not shown]
**Study Design**.

### Sampling and recruitment

Residents with dementia residing in six LTC facilities in Edmonton, and the health care aides working with them, will be recruited to participate in the study. The purposive sample of research participants will be recruited from units which serve cognitively and physically frail older adults rather than units for young disabled people or sub-acute units. Residents that have a diagnosis of dementia and are able to transfer independently, or with the assistance of one person, will be eligible for inclusion in the study. Residents with a serious physical illness or life expectancy less than six months at the time of recruitment will be excluded from the study. We expect that most of the resident participants will be recruited to the study within eight months, however recruitment will continue throughout the study if necessary.

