### Sample Size

The sample size calculation for the number of resident participants is based on the primary outcome measure in the pilot study: the number of sit-to-stands that the resident is able to complete in 30 seconds. Based on our earlier pilot work, we observed residents' ability to maintain and in some instances increase the number of sit-to-stands that they could complete in 30 seconds. We judge an increase of two sit-to-stands completed in 30 seconds to be a meaningful change in the residents' mobility. Based on existing research [10,38,46,47] and the pilot study, the standard deviation of the 30-second sit-to-stand measure is 3.5 sit-to-stands. Thus we will need 49 residents in each of the intervention and the control groups to detect an increase in the number of sit-to-stands that the resident is able to complete in 30 seconds (power = 0.80; 2-tailed; α = 0.05). Assuming an attrition rate of 20% over 6 months we will recruit 60 residents to the intervention group and 60 residents to the control group. We expect to succeed in recruiting and following our sample of 120 residents based on our experience with the pilot study and the experience of [name] who recruited similar samples in two previous studies using similar recruitment methods [4,48].

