
Health care aides will be invited to participate in an in-person, 30 minute interview pertaining to a specific resident if they have been permanent staff members in the facility and have been assigned to work directly with the resident in the past week. Although we considered blinding the research assistant to the intervention this is not possible to maintain because residents and health care aides will undoubtedly refer to the sit-to-stand intervention at some point during their contact with the research assistant. To minimize possible bias the research assistant gathering the outcome data will be independent of the nurse educator who will introduce the mobility intervention to the intervention group. The research assistant will not have access to data that were collected during the previous round of assessments and are unlikely to recall residents' precedent scores. The research assistant will assess all residents for the duration of the study unless unavailable; when the research manager will perform this duty. Therefore inter-rater reliability between the research assistant and the research manager will be assessed at the beginning, middle, and end of data collection.

The extent to which resident participants in the intervention group are exposed to the sit-to-stand activity will be measured using daily *documentation flowsheets *which are part the residents' health record. Managers expect these flowsheets to be completed by health care aides at the end of every day and evening shift. The precise method of incorporating the documentation of the sit-to-stand activity will be tailored to the existing flowsheets in the intervention group facilities. Experience from the pilot study demonstrated that this usual method of documenting personal care using a flowsheet can be an effective and efficient means to assess the sit-to-stand activity adherence of both the health care aides and the residents. We will use this usual documentation as a research data collection tool to minimize the response burden for health care aides. The research assistant will conduct spot checks to compare health care aide performance of the sit-to-stand activity with what they record on the flowsheets. The flowsheets will be collected monthly for the duration of the study.

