### Outcomes

#### Mobility

The sit-to-stand action is a functional activity that has been incorporated into a number of mobility measures including the time to rise without using arms, time for 5 sit-to-stands, time for 10 sit-to-stands, and the number of sit-to-stands completed in 30 seconds. We have chosen to measure mobility using the number of sit-to-stands in 30 seconds because in the frail nursing home population many residents must use their arms to stand [10,38,47,48] and may be unable to complete more than one sit-to-stand. This mobility assessment will be completed by a research assistant using a stopwatch and standard armchair with a standard height of 42 cm. Residents will be instructed to stand up and sit down as many times as possible until they are asked to stop after 30 seconds. In a group of community-dwelling older adults aged 66 to 97 years [47], researchers found evidence for test-retest reliability, criterion validity (comparing the chair stand performance to a measure of lower body strength), and discriminant validity (comparing performance in different age and physical activity groups) with the 30-second sit-to-stand test.

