### Data Analysis

All data will be entered into an SPSS 19 database (IBM, 2010, ^©^IBM Corporation). Ten percent of the data will be double entered to assess the accuracy of data entry. We will compare the baseline characteristics of the LTC facilities, health care aides, and residents in the intervention group with the control group by computing descriptive statistics. Data are structured for each outcome measure (the 30-second sit-to-stand test; the *Functional Independence Measure*; the *Health Utilities Index Mark 2 and 3; *and, the *Quality of Life - Alzheimer's Disease*) to allow a mixed between-within subjects analysis of covariance. Specifically, the between subjects factor consists of the two groups (Control versus Intervention Group) and the within subject factor consists of the repeated measures. The covariates will include baseline characteristics the residents, including age, sex, level of cognitive impairment (Cognitive Performance Scale), extent of depression (MDS Depression Rating Scale), and extent of health instability (CHESS), and characteristics of the LTC facilities including facility size, unit size, ownership model, and quality of the environment (PEAP and ACT). A Multivariate Analysis of Covariance (MANCOVA) will be used to control the experiment-wise error rate for comparisons. Data will be analyzed according to the intention-to-treat principle, i.e. residents who relocate to another setting or who die before completing the six months of follow-up will be included in the data analysis. The extent to which the residents in the intervention facilities actually received the mobility interventions will be assessed using the documentation flowsheet measures to establish a graphical analysis of the covariate-corrected time course of performance on the mobility intervention. These analyses will be conducted using SPSS 19 in consultation with a statistician from the Centre of Health Promotion Studies at the University of Alberta.

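### Two transfer-ability strata are enrolled from six non-randomised facilities, but entry transfer status is not among the named covariates; the 30-second test should also say whether helped stands count

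*Protocol article*

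**What the plan says.** - **Eligibility (Sampling and recruitment).** Residents with dementia who are "able to transfer independently, or with the assistance of one person, will be eligible for inclusion in the study". The sample is purposive.
- **Allocation (Methods/Design; Control group).** The study is quasi-experimental, with three intervention and three control facilities matched on ownership model and size.
- **Outcome behind the sample size (Sample Size).** It is "the number of sit-to-stands that the resident is able to complete in 30 seconds". On the target: "We judge an increase of two sit-to-stands completed in 30 seconds to be a meaningful change in the residents' mobility". On the spread: "the standard deviation of the 30-second sit-to-stand measure is 3.5 sit-to-stands".
- **Test (Outcomes, Mobility).** A research assistant uses a stopwatch and a 42 cm armchair. "Residents will be instructed to stand up and sit down as many times as possible until they are asked to stop after 30 seconds". The section says that many residents in this population need their arms to stand and may not manage more than one stand. It does not mention help from another person.
- **Assessor (Procedure).** Blinding is said to be impossible to maintain. One research assistant assesses everyone, with the research manager as back-up, and inter-rater reliability is checked three times.
- **Covariates (Data Analysis).** "The covariates will include baseline characteristics the residents, including age, sex, level of cognitive impairment (Cognitive Performance Scale"). The list continues with depression, health instability, facility size, unit size, ownership model and the two environment measures. Transfer status, the FIM and the baseline count are not named.

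**The concern.** Transfer ability is the mobility characteristic that decides entry, and it is probably related to how the 30-second count moves over six months. Residents who need one person's help are closest to losing the ability to transfer, which is the loss the study hopes to delay. They may decline faster than independent residents. They may also lose fewer stands, because they start near the floor. Either way, their mean change need not equal that of independent residents.

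Nothing in the design balances the two strata between groups. There is no randomisation, and the matching variables describe facilities rather than residents. If one group holds more assisted residents, part of the difference in change reflects case mix and would be read as an effect of the intervention, or would hide one. The direction cannot be predicted.

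A smaller, related point concerns the test itself. For a resident who usually rises with help, the count depends on whether help is given and whether a helped stand is counted. The article does not say, and the person applying the test knows the group.

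**Working it through.** **1. The plan's own figure.** Inputs from Sample Size: difference 2, SD 3.5, "power = 0.80; 2-tailed; α = 0.05".

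n per group = 2 × [3.5 × (1.960 + 0.842) / 2]² = 48.07, rounded up to 49. This reproduces the stated 49. With 49 per group, SE = 3.5 × √(2/49) = 0.707 and power is 0.807. Recruiting 60 with 20% attrition leaves 48, with power 0.799. The point below does not alter these figures.

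**2. Why the baseline count does not settle the matter.** Let p₁ and p₀ be the shares of assisted residents in the intervention and control groups, and let c_A and c_I be the mean changes in assisted and independent residents with no intervention effect. Then:

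- mean change in group g = p_g × c_A + (1 − p_g) × c_I
- difference between groups = (p₁ − p₀) × (c_A − c_I)

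Starting levels cancel, which is what the repeated-measures comparison provides. The product of the imbalance and the difference in change remains. It is zero only if the shares are equal or the strata change alike.

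**3. Size of the confounding (all inputs assumed).** Take shares of 40% and 20%, an imbalance of 0.20. Take a difference in mean change of 0.5, 1 or 2 stands. The false-positive rate is two-sided at nominal 0.05, with 49 per group, SD 3.5 and residents treated as independent.

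| Difference in change | Shift in group difference | Share of the 2-stand target | False-positive rate |
|---|---|---|---|
| 0.5 | 0.20 × 0.5 = 0.1 | 5% | 0.052 |
| 1 | 0.20 × 1 = 0.2 | 10% | 0.059 |
| 2 | 0.20 × 2 = 0.4 | 20% | 0.087 |

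**4. Size of the helped-stand issue (all inputs assumed).** Let 20% to 40% of residents be assisted. Suppose that for a quarter of them help at follow-up differs between groups, and that it is worth 2 stands:

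- 0.20 × 0.25 × 2 = 0.1
- 0.40 × 0.25 × 2 = 0.2

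The shift is 0.1 to 0.2 stands. If the rule is applied in the same way every time, it is zero. If help is inconsistent but equal between groups (2 stands counted half the time), there is no bias but the SD rises:

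- 20% assisted: √(3.5² + 2² × 0.1 × 0.9) = 3.55, power at 49 per group 0.796
- 40% assisted: √(3.5² + 2² × 0.2 × 0.8) = 3.59, power at 49 per group 0.787

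**The case against.** **The covariates.** Mobility at entry is not ignored: the baseline count is one of the repeated measures, and the FIM grades assistance from 1 to 7, includes transfers and is taken at all three visits. Cognition and health instability, which are covariates, probably track transfer ability in part. The list is also introduced by wording that need not be exhaustive. What stands is that the FIM is an outcome and is not named as a covariate. The baseline count handles level, not rate of change (step 2). A list that names every other resident characteristic leaves out the one used for eligibility.

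**The scoring.** A journal article may leave test detail to a full protocol. The wording already points to unaided performance: the outcome is what the resident can complete, the resident receives the instruction, and no helper appears. Needing one person for a transfer is not shown to mean being unable to rise from a 42 cm armchair using the arms. These points largely stand, which is why scoring is only a secondary clarification here.

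**Stronger readings that a reader might infer.**

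- *The counts are not comparable.* This does not follow from silence. One assessor for nearly all tests, three reliability checks and independence from the nurse educator all limit inconsistency. Reliability checks between two unblinded raters would not, however, reveal help that differs by group, so comparability is not secured either.
- *Withholding earlier data stops the assessor repeating the test in the same way.* The article states "The research assistant will not have access to data that were collected during the previous round of assessments" as a safeguard against bias, and it is a sound one. A fixed scoring rule needs no sight of earlier scores.
- *Power collapses because assisted residents cannot gain.* That assumes a different treatment effect by stratum, which would exist under a perfectly consistent rule. The article gives no basis for it.

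**Conclusion.** The point holds as a low-cost improvement to the analysis. Two mobility strata are enrolled, allocation does not balance them, and the named covariates do not include the variable that defines them. Under the assumed inputs, confounding of the change in the count is 0.1 to 0.4 stands, or 5% to 20% of the 2-stand target. It would be zero if the groups have equal shares or the strata change alike. The article reports neither, so this is an illustration and not an estimate.

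The helped-stand question is worth about 0.1 to 0.2 stands under its own assumptions. Much larger values can be produced only by supposing that help differs between groups by 50 to 100 percentage points, which nothing in the article suggests. The stated sample size is reproduced and is not in question here.

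**What to change.** **Main change (Data Analysis).** Add entry transfer status (independent versus one-person assist) to the resident-level covariates for every outcome. In the repeated-measures model let it interact with time, since a main effect alone adjusts only for level. Report the proportion in each stratum by group at baseline. Screening has to establish transfer ability for every resident, so the cost is recording which of the two applies and one degree of freedom in each contrast. It does not remove other differences between non-randomised facilities.

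**Secondary clarification (Outcomes, Mobility).** State whether a stand completed with another person's hands-on help counts, and what is scored for a resident who cannot rise without it. Record help and arm use at each test. The cost is a sentence or two and a tick-box per test. The choice has a trade-off that the sponsor should weigh: not counting helped stands gives more zeros and hides progress from heavy to light help, while counting them makes the score depend on the helper. Earlier scores should stay withheld from the assessor.
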